### Recording of adverse events and serious adverse events

From the point of signing the informed consent form (ICF) to the first administration of study medication, any worsening of an existing or new medical condition must be recorded on the Medical History CRF page. Following administration of study medication up to the week 8 (Termination), any worsening of an existing or new medical condition must be recorded as an AE on the CRF. The investigator should review all documentation (e.g., hospital progress notes, laboratory, and diagnostic reports) relative to the event being reported. The investigator will then record all relevant information regarding an AE/SAE on the appropriate CRF page. The investigator will evaluate AEs using the following guidelines:

- Description of event (if the event consists of a cluster of signs and symptoms, a diagnosis should be recorded [e.g., flu syndrome] rather than each sign and symptom)
- Onset date and time
- Stop date and time
- Intensity should be described according to the Division of AIDS Table for Grading Severity of Adult and Pediatric Adverse Events, December 2004 (Appendix 16.1) as MILD (Grade 1), MODERATE (Grade 2), SEVERE (Grade 3), or life threatening (Grade 4). Intensity is defined as one of the following:
- Mild: transient or mild discomfort; no limitation in activity; no medical intervention/therapy required
- Moderate: mild to moderate limitation in activity- some assistance may be needed; no or minimal medical intervention/therapy required
- Severe: marked limitation in activity, some assistance usually required; medical intervention/therapy required, hospitalizations possible
- Life-threatening: extreme limitation in activity, significant assistance required; significant medical intervention/therapy required; hospitalization or hospice care probable

It is important to distinguish between SAEs and severe AEs. Severity is a measure of intensity, whereas seriousness is defined by the criteria provided in Section 9.1.2. An AE of severe intensity need not necessarily be considered serious. For example, a migraine headache that incapacitates a subject for many hours may be considered a severe AE, whereas a stroke that results in a limited degree of disability may be considered mild, but should be reported as an SAE. If any parameter within a record of an Adverse Event changes, a fresh record should be made in the CRF. For example, but not limited to, where the severity of the AE increases, the AE should be recorded as resolved at the existing severity level and re-entered into the CRF with a new start date reflecting the first date of the increased severity.

- Seriousness (see definition of an SAE, Section 9.1.2)

The investigator must record whether or not the AE meets the definition of serious. If the event is serious, the Investigator must complete an SAE Report Form.

- Relationship to study drug

The investigator must make a causality assessment for all AEs and must decide whether there is a reasonable possibility that the AE may have been caused by the study drug. If there is any valid reason for suspecting that there is a causal relationship between the AE and the study drug, the AE should be judged “possibly related,” “probably related,” or “definitely related” to study drug. Unless an AE can be excluded from causality, it must be judged “possibly related” to study drug rather than “not related” to study drug.

- Outcome

Outcome of AEs should be recorded as resolved, resolved with sequelae, not resolved, or fatal based on the status of the AE at discontinuation from the study. If an AE is not resolved at the time of discontinuation, the AE should be followed until it is resolved (returns to normal or pretreatment values) or stabilized, or until it is judged by the Investigator to be no longer clinically significant.

- Action taken (none, required treatment, reduction of dose, or permanent discontinuation of study drug). *All applicable actions taken should be recorded.*

### Follow-up of adverse events and serious adverse events

All AEs and SAEs must be followed until they are resolved (return to normal or pretreatment values) or stabilized, or until they are judged by the Investigator to be no longer clinically significant. Supplemental measurements and/or evaluations may be necessary to fully investigate the nature and/or causality of an AE or SAE. This may include additional laboratory tests, diagnostic procedures, or consultation with other healthcare professionals. If the subject dies, any findings (including histopathology) must be provided to the Investigational drug substance suppliers.

### Reporting of all serious adverse events and any adverse events resulting in study discontinuation

The investigator will promptly report all SAEs to the regulatory and ethical agencies.

Any SAE, regardless of expectedness or causality, must be reported by telephone and by faxing the completed SAE Report Form to the investigational drug substance suppliers within 24 hours of the investigator or any other site personnel’s knowledge of the event. In addition, any AE resulting in permanent study discontinuation for a subject, even if not serious, must be reported immediately to the Investigational drug substance suppliers. An updated SAE Report Form should be forwarded to the investigational drug substance suppliers within 24 hours of receipt of the new/updated information.

Table 3 Serious Adverse Event Reporting Requirements

|  | INITIAL REPORTS | **FOLLOW‑UP REPORTS** |
| --- | --- | --- |
| REPORTING REQUIREMENTS | **24 hours**  Telephone and fully completed SAE Report Form to the Investigational drug substance suppliers | **24 hours**  Updated SAE Report Form to the Investigational drug substance suppliers |

For investigational drugs, an AE is judged expected if its description agrees in nature, severity, frequency, and specificity with the description of events in the current Investigator’s Brochure. For marketed drugs, an AE is judged expected if it is listed in the current package insert or the current product’s packaging materials for the country concerned.

### Post-study adverse events or serious adverse events

Investigators are not obligated to actively seek AEs or SAEs after the follow-up period. However, the investigator should promptly notify the investigational drug substance suppliers if the investigator learns of any SAE or death of a study subject within 30 days after a subject has been discontinued from the study, and such event(s) is (are) reasonably related to the study drug.

Investigators should promptly notify the investigational drug substance suppliers if they become aware of a former study participant who is one of the parents of a subsequently conceived child with a congenital anomaly.

## Overdose

An overdose is not recorded as an AE unless symptoms of the overdose occur, in which case the symptoms are recorded as AEs and attributed to the (over)dose of study drug.

# data collectionData Collection

## Data collection

Subject data will be collected on CRFs and source documents at the clinical site. Prior to the start of the study, the investigator will complete a site personnel log showing the signatures and handwritten initials of all individuals who are authorized to make or change entries on CRFs. All required data are to be recorded on the CRF.

Completed CRFs will be reviewed by the study monitor to ensure completeness and consistency. The study monitor will subject all CRF data to 100% source verification and audit to ensure adequate quality control and assurance of subject data. Any discrepancies found during the CRF review are to be clarified by the investigator.

The investigator must sign and date a declaration on the CRF attesting to his/her responsibility for the quality of all data recorded, and that the data represents a complete and accurate record of each subject’s participation in the study. The original completed CRF will be returned to the investigational drug substance suppliers, and a copy will be retained by the investigator.

## Correcting the case report forms

Errors must be corrected by drawing a single line through the incorrect entry and by writing the new value as close to the original as possible. The correction must then be and dated by an authorized individual.

## Data processing

The completed original CRF will be signed and dated by the investigator and transmitted to the investigational drug substance suppliers (or designee) after each subject completes study participation. A duplicate signed copy of the CRF and a record of the laboratory data for each subject will be retained at the site.

A database will be constructed from the CRFs and the data will be validated both manually and electronically. Clarification of data will be requested from the study site as required.

# sTATISTICal methods and planned analyses

This is a single blinded randomized pilot study designed to investigate the safety and efficacy of intranasal administration of three different dose-levels of Vacc-4x using Endocine as an adjuvant.

## Determination of sample size

It is decided that 6 subjects should be included in each of the four study arms. As this is a pilot study, the sample size has primarily been determined to provide descriptive statistics for the safety and efficacy parameters.

## Randomization

Subjects who meet the entry criteria will be randomized into one of the four study arms by using SAS version 9.2.

## Populations to be analyzed

The following populations will be used in the analysis:

Intention to treat (ITT): Consistent with the intent-to-treat principle, all subjects receiving treatment will be included in the safety and efficacy analyses (full analysis population as defined by ICH-E9).

Per protocol (PP): All ITT subjects who receive the full immunization and who do not incur any major protocol violations that would challenge the validity of their data will be included in an additional analysis of main the efficacy parameters.

## Handling of missing data

Missing data will not be imputed and all summary statistics will be reported based upon observed data.

## Subject accountability

The study disposition of all randomized study subjects will be summarized. Subjects who discontinued study drug prematurely or withdrew from the study will also be summarized and listed with a description of the reason for early termination/withdrawal.

### Treatment compliance

Subject compliance with study drug dosing will be assessed by the study personnel and compliance will be summarized using descriptive statistics.

## Statistical methods

Analyses will be based upon an intent-to-treat approach. In general continuous variables will be described using number of observations (N), mean, median, standard deviation (SD), minimum (min), maximum (max), Categorical data will be presented using counts (N) and percentages (%). Subjects without a baseline or a post-baseline assessment for a particular endpoint will not be included in the analysis of change from baseline for that endpoint. All statistical analyses will be performed using SAS Software Version 9.2 or higher. P-values will be reported as 2-sided p-values. All confidence intervals will be reported using traditional 95% two-sided intervals. No adjustment for multiple comparisons will be made.

### Analysis of demographic and subject characteristics

Demographic and subject characteristics will be summarized using descriptive statistics.

### Safety analysis

The primary objective of this study is to investigate the safety of intra-nasal administration of three different dose-levels of Vacc-4x using Endocine as an adjuvant.

#### Adverse events

For presentation, AE verbatim text will be coded into a Medical Dictionary for Regulatory Activities Terminology (MedDRA) term, and classified by System Organ Class (SOC) and preferred term prior to analysis. AEs will then be summarized and grouped by SOC and preferred term. AEs with onset on or after the start of study medication are considered treatment emergent. AEs reported prior to treatment administration will be reported separately from treatment emergent AEs. A cross reference listing, which will relate SOC, preferred term, and verbatim text will be provided.

In addition, summaries will be provided by incidence, severity (mild, moderate, severe), and relationship to study medication (Related, Unrelated). "Possibly Related," "Probably Related," and "Definitely Related" will be grouped as “Related.”

SAEs and AEs leading to discontinuation will be summarized and listed.

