### Dosage and administration of study drug

Vacc-4x is administered intranasal as a mixture of Vacc-4x peptides and the adjuvant Endocine.

The study includes four groups:

***A low dose group***: 80 µg Vacc-4x (20 µg pr. peptide) divided into two administrations;

40 µg Vacc-4x in 150 µl Endocine for each nostril.

***A medium dose group***: 400 µg Vacc-4x (100 µg pr. peptide) divided into two administrations;

200 µg Vacc-4x in 150 µl Endocine for each nostril.

***A high dose group***: 1200 µg Vacc-4x (300 µg pr. peptide) divided into two administrations;

600 µg Vacc-4x in 150 µl Endocine for each nostril.

***A zero dose group***: Only adjuvant divided into two administrations;

150 µl Endocine for each nostril.

The drug will be administered four times with one week interval; at week 1, week 2, week 3 and week 4.

A DTH test (Vacc-4x 400 µg intra-dermal) will be done at week 8.

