#### Visit 6 (Week 8 – Day 50 (3)) – END OF STUDY

The following assessments will be performed:

- Review of concomitant medications and AEs
- Physical examination, including weight
- Vital signs
- Clinical chemistry and hematology
- Viral load (HIV-1 RNA) and CD4 counts
- T-cell responses
- Collection of secret from nose and rectum
- Collection of urine
- DTH test (immunization to occur on designated day; test to be evaluated 48 hours after immunization)

The subject should remain in the clinic for 30 min after the administration of the DTH test to be monitored for adverse reactions to the DTH test.

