## Efficacy assessments

### Delayed type hypersensitivity test administration

DTH testing will be performed at the last visit (Week 8). An injection of 0.1mL of a 4.0mg/mL Vacc‑4x should be administered intradermally at the front of left arm. The DTH test should be performed by the investigator, study nurse, or other clinician experienced in the techniques of intradermal injection. The DTH test results will be evaluated 48 hours after the tests are performed. For each DTH test, evaluation of the injection site at 48 hours will include palpable skin induration and skin erythema. A positive DTH test is defined as an area 10mm2 (either induration or erythema). Study personnel will record DTH results in the subject’s source documents and transcribe them into the CRF. For subjects whose DTH reactions are measured by someone other than study personnel, the investigator is responsible for collecting and recording the result; use of a prepared form completed by the alternative evaluator at the time of the reading is strongly recommended and should be filed with the subject’s source documents.

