# Adverse Event Management

## Non‑serious and serious adverse events

The investigator is responsible for the detection and documentation of events meeting the criteria and definition of an AE or SAE as provided in this protocol (see below). All AEs and SAEs that occur from the time written informed consent is obtained until completion of the study, week 8, will be entered on the appropriate CRF page (see Section 9.1.4). Information to be collected includes the description, date and time of onset, intensity, duration, causality, and outcome of the event. Even if the AE is assessed by the investigator as not reasonably attributable to study drug, its occurrence must be recorded in the source documents and reported on the CRF.

Periodically during the study, after the subject has had an opportunity to spontaneously mention any problems, the investigator should inquire about the occurrence of AEs. The following are examples of open‑ended questions that may be used to obtain this information:

- “How are you feeling?”
- “Have you had any medical problems since your last visit/assessment?”
- “Have you taken any new medicines, other than those given to you in this study, since your last visit/assessment?”

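### Treatment-emergent AEs have no end point, so reactions to the Week 8 intradermal Vacc-4x skin test enter the intranasal safety totals of every arm, including adjuvant-only

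*Protocol*

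**What the plan says.** - **Treatment emergence** (Protocol 11.6.2, Adverse events): "AEs with onset on or after the start of study medication are considered treatment emergent". Pre-treatment AEs are reported apart. No end date, route or procedure limits the rule. The summaries are by SOC and preferred term, incidence, severity, and Related or Unrelated to study medication.
- **AE window** (9.1): "All AEs and SAEs that occur from the time written informed consent is obtained until completion of the study, week 8" are to be entered on the CRF. Section 9.1.4 agrees: from the first dose to termination at Week 8, anything new or worse counts as an AE.
- **Skin test** (6.1.2): "A DTH test (Vacc-4x 400 µg intra-dermal) will be done at week 8". Section 8.2.1 gives the volume and concentration: "An injection of 0.1mL of a 4.0mg/mL". No arm is exempted.
- **Visit 6** (7.3.3): subjects stay 30 minutes "to be monitored for adverse reactions to the DTH test", with the "test to be evaluated 48 hours after immunization".
- **Flow chart** (4.1, Table 2): the closing column, Days 50-53, is marked for both the DTH test and adverse events.
- **Efficacy use** (3.2.2 and 8.2.1): induration and erythema areas, and a positivity threshold, are efficacy results. The protocol does not say whether they are also AEs.

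**The concern.** The primary objective is the safety of intranasal Vacc-4x with Endocine at three dose levels, with an Endocine-only arm as the comparator. Under the rule as written, an adverse reaction to an intradermal injection of Vacc-4x is a treatment-emergent AE of whichever intranasal arm the subject belongs to. The adjuvant-only arm, which should show what happens without Vacc-4x, can then contribute Vacc-4x reactions.

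This does not cancel across arms. If DTH-caused AEs are equally frequent everywhere, they raise all totals and shrink the difference from the adjuvant-only arm. If they are more frequent in immunised subjects, which is the kind of difference a DTH test is meant to detect, they add a difference that intranasal dosing did not cause. With six subjects per arm, each reclassified subject moves an arm's percentage by 1/6, about 17 points.

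**Working it through.** **Inputs from the protocol.** DTH injection 0.1 mL at 4.0 mg/mL (8.2.1); four intranasal doses of 0, 80, 400 or 1200 µg (6.1.2); 6 subjects per arm (11.1).

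**The plan's own figure.** 0.1 mL × 4.0 mg/mL = 0.4 mg = 400 µg, which matches 6.1.2.

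**Timing.** AE recording runs to Week 8 and the injection is given at the Week 8 visit. The 30-minute observation falls inside the window. The 48-hour reading probably does too, because Table 2 marks AEs in the Day 50-53 column, but no text fixes whether termination means the injection day or the reading.

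**Exposure to Vacc-4x by route** (cumulative, four intranasal doses against one DTH injection):

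| Arm | Intranasal | DTH | DTH share |
| --- | --- | --- | --- |
| Zero | 0 µg | 400 µg | 100% |
| Low | 4 × 80 = 320 µg | 400 µg | 400/720 = 56% |
| Medium | 4 × 400 = 1600 µg | 400 µg | 400/2000 = 20% |
| High | 4 × 1200 = 4800 µg | 400 µg | 400/5200 = 8% |

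The amounts describe exposure only; they do not predict event rates by either route.

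**Effect on an any-AE percentage.** Let p be the risk of an AE before the DTH injection and q the risk of a DTH-caused AE. Both are assumptions, since the protocol gives neither, and independence is also assumed. The tabulated risk is 1 − (1 − p)(1 − q). If q is the same in both arms, the risk difference is multiplied by (1 − q).

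Take p = 1/6 (17%) for zero dose and 1/2 (50%) for high dose, a true difference of 33 points:

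- q = 10%: 1 − (5/6)(0.9) = 25% and 1 − (1/2)(0.9) = 55%. Difference 30 points.
- q = 50%: 1 − (5/6)(0.5) = 58% and 1 − (1/2)(0.5) = 75%. Difference 17 points.
- q = 80%: 1 − (5/6)(0.2) = 83% and 1 − (1/2)(0.2) = 90%. Difference 7 points.

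With equal p = 1/6 in both arms but q = 30% in zero dose and 80% in an immunised arm: 1 − (5/6)(0.7) = 42% and 1 − (5/6)(0.2) = 83%. Difference 42 points, none of it from intranasal dosing.

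The first line represents adverse reactions other than the skin reading. The other three are plausible only if induration and erythema are themselves entered as AEs.

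**Chance that the adjuvant-only arm is affected at all.** P(at least one DTH-caused AE among 6) = 1 − (1 − q)^6. For q = 10%, 25% and 50% this is 47%, 82% and 98%. Even a low rate has about an even chance of putting a Vacc-4x reaction into the arm assigned no Vacc-4x.

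**The case against.** Five points can be made for the plan.

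1. **The skin reading is handled as efficacy.** Sections 3.2.2 and 8.2.1 give induration and erythema their own measurement, threshold and CRF entry, and nothing says they are also AEs. This stands and limits the size. A reader might infer that the tables will be swamped, with a 33-point difference cut to 7 or a 42-point artefact created. The protocol does not support that unless the readout is double-counted. It does not rule double-counting out either.

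2. **Nasal events stay visible.** A reader might infer that an intranasal signal could be hidden. The expected intranasal events are local nasal irritation (2.7), application-site reactions in the nose are reported as their own category (5.4.1), and AEs are shown by preferred term. An arm reaction does not mask a nasal term. This stands; what remains exposed is overall totals, Related counts and systemic terms.

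3. **Relatedness is not settled.** It is tempting to say DTH reactions will be classed as Related because the agent is Vacc-4x. Section 9.1.4 does require at least a possible relation unless causality can be excluded, and 6.1.2 lists the DTH test under study-drug dosage. But the visit schedules distinguish giving study drug from giving the DTH test. The text permits either judgement, which is a reason to ask the question separately.

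4. **A SAP could split by onset.** Onset date and time are recorded, so with 24 subjects a split is feasible. This stands in part: the protocol itself states the treatment-emergent rule, and a later split by onset cannot recover a causality judgement that the CRF never asked for.

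5. **The safety analysis is descriptive.** No between-arm safety test is specified, and 11.6.2 does not say in words that AE tables are by arm. By-arm is still the natural reading of a four-arm trial with an adjuvant-only control, and descriptive percentages will be read as a comparison.

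**Conclusion.** The concern holds in a limited form. Following 11.6.2 as written places adverse reactions to the Week 8 intradermal Vacc-4x injection in the overall AE totals, and in the Related counts where so judged, of arms meant to describe intranasal safety. The adjuvant-only arm is included. This is certain for reactions during the 30-minute observation and probable up to the 48-hour reading.

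The size cannot be known from the protocol. If the skin readout remains efficacy data only, the distortion is probably modest: about 3 points off a 33-point difference at an assumed 10% rate, although one subject is worth about 17 points. It is large only if the readout is also entered as an AE. The protocol does not show that an intranasal signal would be hidden. The change is still worth making, because the affected tables serve the primary objective and the remedy costs little.

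**What to change.** In 11.6.2:

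- End the primary intranasal treatment-emergent period immediately before the DTH injection.
- Tabulate AEs with onset from the DTH injection onward separately by arm, and keep them in the full AE listing.
- State that DTH induration and erythema are efficacy data and are not AEs in the primary tables.

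On the CRF, record causality separately for the intranasal product and for the DTH injection.

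The cost is a few sentences, one extra table and one CRF field, with no added visits or subjects. The downside is that a late AE caused by intranasal dosing but starting after the DTH injection would appear in the separate table; the full listing and the separate causality entry keep it traceable.
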